# Effect of probiotic supplementation on in-hospital mortality in patients with acute myocardial infarction: a study protocol for an open-label, randomized, controlled, superiority clinical trial

**DOI:** 10.1186/s13063-023-07443-5

**Published:** 2023-06-24

**Keywords:** Probiotics, Acute myocardial infarction, Major adverse cardiovascular events (MACE), Mortality, Randomized controlled trial

## Abstract

**Background:**

Recent studies have demonstrated a correlation between intestinal flora and the severity of myocardial infarction as well as post-myocardial infarction repair. However, few studies have investigated whether probiotics reduce mortality and improve cardiovascular outcomes in patients with acute myocardial infarction. In this study, we will conduct a randomized controlled trial (RCT) to evaluate the effect of probiotics on in-hospital mortality and the incidence of major adverse cardiovascular events (MACE) in patients with acute myocardial infarction (AMI).

**Methods:**

This is an open-label, randomized, controlled, superiority clinical trial involving 2594 adult patients who were diagnosed with acute myocardial infarction. Patients will be randomized to (1) receive bifidobacteria triple viable capsule (*Bifidobacterium longum*, *Lactobacillus acidophilu*s, and *Enterococcus faecalis*) 840 mg, twice a day, plus standard treatment strategy during the hospital stay, for a maximum of 30 days, or (2) receive the standard treatment strategy and will not take the bifidobacterium triple live capsule. The primary outcome was in-hospital all-cause mortality.

**Discussion:**

The purpose of this clinical trial is to determine whether probiotics can reduce in-hospital mortality and improve prognosis in patients with AMI, and the results will provide evidence for probiotics as a complementary treatment for AMI.

**Trial registration:**

Chinese Clinical Trials Registry ChiCTR2000038797. Registered on 2 October 2020.

**Supplementary Information:**

The online version contains supplementary material available at 10.1186/s13063-023-07443-5.

## Background

Acute myocardial infarction (AMI) is a severe form of coronary heart disease, and its high morbidity and mortality pose the main threat to human life and health. The incidence of adverse cardiovascular events after AMI, such as heart failure and arrhythmias, is associated with a substantially higher risk of death [1, 2]. In recent decades, with the rise of reperfusion therapy and the standardization of treatment for AMI, the mortality rate has decreased significantly. However, a significant inpatient mortality rate remains and can be as high as 8.9% [3], and the incidence of heart failure after acute myocardial infarction during hospitalization ranged from 40.2 to 40.5% [4]. Therefore, the treatment of acute myocardial infarction needs to be further optimized.

Recent studies have shown an important link between intestinal flora and the severity of myocardial infarction and heart repair after myocardial infarction [5, 6]. Intestinal disorders and bacterial translocations play an important role in the development of myocardial infarction and in cardiovascular events after infarction [7]. Patients with acute coronary syndrome (ACS) had typical intestinal microflora disorders, which were manifested as increased harmful bacteria and decreased beneficial bacteria [8]. Many animal studies have confirmed that probiotics can reduce the size of myocardial infarction and reduce cardiac hypertrophy [5, 9]. Several clinical trials have also reported that probiotics can reduce ventricular remodeling after MI and improve ventricular systolic function in patients with heart failure [10, 11], which imply that probiotic supplementation may improve the prognosis of acute myocardial infarction. However, it has not been reported whether probiotics can reduce the incidence of adverse cardiovascular events and mortality in patients with MI in the hospital. In this study, we will evaluate the effect of probiotics on in-hospital mortality and the incidence of major adverse cardiovascular events (MACE) in patients with AMI to understand whether probiotics have a protective effect on patients with acute myocardial infarction through a randomized controlled trial (RCT).

## Methods

### Study design

This prospective trial will be a single-center, open-label, randomized, controlled, superiority clinical trial. A total of 2594 patients with AMI (both acute ST-segment elevation and non-ST-segment elevation myocardial infarction) will be recruited and randomized in a 1:1 fashion to one of the two treatment arms from October 2020 through October 2025. The protocol was designed according to the Standard Protocol Items: Recommendations for Interventional Trials (SPIRIT) 2013 Statement [12]. The protocol was designed in accordance with the SPIRIT 2013 Statement (Standard Protocol Items: Recommendations for Interventional Trials). The SPIRIT Checklist for this protocol is detailed in the Supplementary Material, Additional file 2.

### Ethics issues

Ethical approval for the study has been obtained from the Committee of Ethics of the First Affiliated Hospital of Shantou University Medical College (Number: B-2020–165-FS).

### Study hypothesis and objectives

Studies have shown that patients with AMI have certain intestinal flora disorder and impaired intestinal barrier function [8]. When myocardial infarction occurs, intestinal bacteria and metabolites translocate into the systemic circulation, causing metabolic endotoxemia and stimulating systemic low-grade inflammation, thereby affecting the repair of the heart after myocardial infarction and the occurrence of adverse time after myocardial infarction [13]. Therefore, we hypothesized that early probiotic supplementation after AMI could have a positive effect on the heart by repairing the gut barrier, reducing endotoxemia and systemic inflammation.

The primary objective of this trial is to determine the effect of probiotics on in-hospital mortality of AMI patients. The secondary objective is to investigate whether probiotics can reduce the incidence of major adverse cardiovascular events (including heart failure, malignant arrhythmias, cardiogenic shock, myocardial infarction-related mechanical complications, and recurrent myocardial infarction) and improve ventricular systolic function in patients with AMI; echocardiography will be measured at baseline and after treatment.

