#### Secondary outcome

Secondary outcomes will be clinical complications and laboratory results serve as surrogate end-points for prognosis. The secondary outcomes include the following:The incidence of MACE (including heart failure, malignant arrhythmias, cardiogenic shock, cardiogenic death, and recurrent myocardial infarction) during hospitalization or at 30-day follow-upThe incidence of myocardial infarction-related mechanical complications during hospitalization or at 30-day follow-upThe difference between the trial groups in left ventricular ejection (LVEF) measured by echocardiography at baseline, 7th day, and 30th day

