### Definition

In this study, MACE is defined as heart failure, malignant arrhythmias, cardiogenic shock, cardiac death, and recurrent myocardial infarction.According to the AHA/ACC/HFSA Guidelines for Managing Heart Failure [15], the diagnosis of heart failure is mainly based on clinical manifestations and physical examination: (1) typical clinical manifestations of new-onset heart failure (such as dyspnea, ankle edema, fatigue), (2) moist rales could be heard in more than one-third of the lung fields, (3) chest X-ray showed non-cardiac pulmonary edema or pulmonary obstruction, and (4) abnormal levels of brain natriuretic peptide or B-type natriuretic peptide precursor.Malignant arrhythmias are defined as atrial fibrillation/flutter, ventricular tachycardia, and high-degreee atrioventricular block.The criteria for cardiogenic shock include less than 90 mmHg systolic blood pressure, continuing for at least 30 min, clinical signs of pulmonary congestion, and organ perfusion for signs of damage to at least one of the following performance: the mental state changes, skin and limbs cold and wet, oliguria, and urinate less than 30 ml per hour.Cardiac death is defined as death from any of several cardiac causes.Recurring myocardial infarction is defined as another myocardial infarction 28 days after the onset of acute myocardial infarction, with ST-elevation ≥ 1 mm recurs, or new pathogomonic Q waves appear in at least two contiguous leads, especially when accompanied by symptoms of ischemia.Myocardial infarction-related mechanical complications include cardiac rupture, ventricular septal rupture, and papillary muscle rupture.

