The above results indicate that probiotics may reduce the incidence of cardiovascular adverse events and mortality by reducing myocardial infarction area expansion and reducing ventricular remodeling. However, to our knowledge, there are no data to report whether probiotics can reduce mortality or adverse events in patients with myocardial infarction. Therefore, we will further demonstrate the effect of probiotics on the prognosis of patients with acute myocardial infarction through an RCT by evaluating in-hospital mortality and incidence of MACE (acute heart failure, malignant arrhythmia, cardiogenic shock) and myocardial infarction-related mechanical complications in patients.

Our study has some limitations. First, this is a single-center clinical trial, and the results are not representative of all patients with AMI. Secondly, bifidobacterium triple live capsule is a compound microecological agent containing three kinds of bacteria. Although it can help regulate intestinal flora, we cannot explain which bacteria are effective. Furthermore, we do not conduct microflora analysis on the blood and feces of patients in this study. If the initial results are positive, we plan to analyze blood and feces samples from AMI patients on the first day of hospitalization and after treatment to further confirm the influence of probiotics on the intestinal microflora of AMI patients.

In summary, the primary therapeutic goal of modern cardiology is to reduce inflammation and myocardial necrosis and to enhance cardiac repair after myocardial infarction [28]. If the results of this investigation show are effective, it will provide strong evidence of the value of probiotics as an intervention to reduce mortality and improve outcomes in patients with AMI.

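### The secondary objective and the MACE endpoint list different components, and two of the written event criteria (malignant arrhythmia, heart failure) are misstated

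*Protocol article*

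**What the plan says.** The protocol article lists the components of MACE in four places.

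- **Study hypothesis and objectives:** "including heart failure, malignant arrhythmias, cardiogenic shock, myocardial infarction-related mechanical complications, and recurrent myocardial infarction".
- **Secondary outcome:** "including heart failure, malignant arrhythmias, cardiogenic shock, cardiogenic death, and recurrent myocardial infarction". The next item in that section makes mechanical complications a secondary outcome of their own.
- **Definition:** "MACE is defined as heart failure, malignant arrhythmias, cardiogenic shock, cardiac death, and recurrent myocardial infarction".
- **Discussion:** "incidence of MACE (acute heart failure, malignant arrhythmia, cardiogenic shock) and myocardial infarction-related mechanical complications in patients".

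The Definition section then sets criteria for the components. For arrhythmia: "Malignant arrhythmias are defined as atrial fibrillation/flutter, ventricular tachycardia, and high-degreee atrioventricular block". For heart failure it gives four numbered items, the third being "chest X-ray showed non-cardiac pulmonary edema or pulmonary obstruction". It does not say how many of the four are needed. Heart failure has to be of new onset. Malignant arrhythmia and cardiogenic shock carry no onset rule.

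The Blinding section says that participants, investigators, outcome assessors and analysts all know the allocation.

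**The concern.** The objective says which question the trial will answer about MACE, and the outcome section says what will be counted. Here they are two different composites. A patient who dies of a cardiac cause with no other component is an event under one and not under the other. A patient with only a mechanical complication is classified the opposite way.

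The two faulty criteria affect MACE whichever list is used. The arrhythmia definition is closed: it says what malignant arrhythmias are and offers no examples or catch-all. Ventricular fibrillation is therefore outside it. The heart-failure item asks for a sign that, by its own adjective, does not come from the heart.

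Exact criteria matter more than usual in this trial because every assessor knows the treatment. Written rules are the main protection against classification that follows allocation. Where a rule is contradictory, the assessor has to choose a reading with the allocation in view.

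**Working it through.** **1. The lists side by side.** Each row is a patient with that finding and no other.

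| Patient | Objectives | Secondary outcome and Definition | Discussion |
|---|---|---|---|
| Heart failure, listed arrhythmia or shock | event | event | event |
| Recurrent infarction | event | event | not listed |
| Cardiac death | not listed | event | not listed |
| Mechanical complication, survived | event | separate outcome | named apart from MACE |
| Ventricular fibrillation, survived | no event | no event | no event |

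The Secondary outcome and Definition sections agree with each other. The substantive conflict is between them and the objective, in rows 3 and 4. The last row follows from the arrhythmia criterion and is the same under every list.

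**2. What the list conflict does to the MACE rate.** Let d be the proportion with cardiac death and no other component of either list. Let m be the proportion with a mechanical complication, no cardiac death and no shared component. Then

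rate (outcome list) − rate (objective list) = d − m.

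The documents give neither d nor m, so the difference cannot be computed.

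**3. The heart-failure item under either counting rule.** If any one of the four items is enough, non-cardiac oedema is scored as heart failure. If all four are needed, a patient with true cardiogenic oedema does not meet the oedema part of item 3. The wording is wrong under both rules. The article does not say which applies.

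**4. Does the planned sample size depend on MACE?** Inputs from the Sample size section: mortality 8.9% and 5.34%, power 90%, two-sided alpha 0.05, dropout 15%, log-rank test with the Freedman method.

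- HR = ln(1 − 0.0534) / ln(1 − 0.089) = 0.589.
- Events = [(1 + HR)/(1 − HR)]² × (1.960 + 1.282)² = 157.
- Mean event rate = (0.089 + 0.0534)/2 = 0.0712, so n per arm = 157 / 0.0712 / 2 = 1102.5. The plan states 1102.
- 1102 / 0.85 = 1296.5, rounded up to 1297 per arm, or 2594 in total.

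The plan's figure is reproduced and uses mortality only.

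**5. Illustration of what misclassification could cost MACE.** These inputs are assumptions. The control MACE rate is set at 40.2%, the lower of the in-hospital heart-failure rates in the Background ("the incidence of heart failure after acute myocardial infarction during hospitalization ranged from 40.2 to 40.5" percent). There are 1102 patients per arm, alpha is 0.05 two-sided, and misclassification is equal in both arms. Power is for two proportions, with a pooled variance under the null and an unpooled variance under the alternative:

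power = Φ{[(p1 − p2) − 1.96 √(2p̄(1 − p̄)/n)] / √([p1(1 − p1) + p2(1 − p2)]/n)}.

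For a relative risk of 0.85, p1 = 0.402 and p2 = 0.402 × 0.85 = 0.3417, which gives 83%. If 5% of non-events are falsely counted, p1 = 0.402 + 0.598 × 0.05 = 0.4319 and p2 = 0.3417 + 0.6583 × 0.05 = 0.3746, which gives 78%.

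| True relative risk | No error | 5% / 10% of non-events added | 5% / 10% of events missed |
|---|---|---|---|
| 0.80 | 98% | 96% / 93% | 97% / 95% |
| 0.85 | 83% | 78% / 73% | 80% / 77% |
| 0.90 | 49% | 44% / 40% | 46% / 43% |

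The table shows direction and rough scale only. The documents give no misclassification rates.

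**The case against.** The strongest reply is that the governing text is consistent. The Definition section states what MACE is in this study, the Secondary outcome section lists the same five components, and an analyst would follow those. The Discussion list ("MACE (acute heart failure, malignant arrhythmia, cardiogenic shock") is plausibly shorthand, and it too names mechanical complications apart from MACE. This stands, and it confines the list conflict to the objective. It does not remove it. The word including in the objective might excuse leaving death out, but it cannot excuse putting in a component that the Definition leaves out.

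A second reply is that non-cardiac is a slip of wording, and that the section rests the diagnosis mainly on clinical findings and examination. That is likely. A reader might infer that non-cardiac oedema alone makes a patient a heart-failure case, or that the error touches most MACE events because heart failure is common. The documents support neither. No text lets the X-ray sign qualify alone, and 40.2 to 40.5% is a background rate, not the share of diagnoses that rest on this sign.

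Third, fatal ventricular fibrillation is not lost, since it counts as cardiac death in the operative list and as death in the primary outcome. That is right, and the gap is limited to survived episodes with no other component.

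Fourth, a reader might take the mark for MACE at day 0 in Table 1 to mean that events present before randomisation are counted. The same column marks all-cause death and serious adverse events, so it reads more naturally as the start of surveillance. Recurrent infarction is later than the index event by definition, and death cannot precede randomisation. What remains is that arrhythmia and shock have no stated onset rule.

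**Conclusion.** The point holds as a defect of definition. The objective and the endpoint name different composites. The arrhythmia criterion omits ventricular fibrillation, and one heart-failure item contradicts the condition it is meant to identify. Followed literally, the criteria misclassify some patients in a trial where every assessor knows the allocation.

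The size cannot be computed from the documents. It is tempting to say that up to 8.9% of controls and 5.34% of probiotic patients could die and be scored free of MACE under the objective's list. Those figures are planned all-cause mortality, whereas the operative list adds only cardiac death. Reaching them would also require that no patient who died had heart failure, shock, a listed arrhythmia, a mechanical complication or a recurrent infarction. They are at most a ceiling on d, and they say nothing about m. Nor do the documents support calling MACE the main secondary outcome: it is listed first, but no hierarchy is stated.

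The primary outcome and the sample size are unaffected. The correction should be made, but it does not threaten the trial's main comparison. These conclusions rest on the article's wording; a fuller protocol or the case report forms might already resolve some of it.

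**What to change.** Make one dated amendment, by the route in the Auditing and amendment section, before any further unblinded review of outcomes:

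1. Use the component list of the Secondary outcome and Definition sections throughout. Align the objective and the Discussion with it, and keep mechanical complications as a separate outcome.
2. Add ventricular fibrillation to the definition of malignant arrhythmias.
3. Correct non-cardiac to cardiogenic in the heart-failure X-ray item.
4. State that malignant arrhythmia and cardiogenic shock count only when they begin after randomisation.

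The cost is the amendment and a re-check of events already recorded. Recruitment is under way and assessors are unblinded, so the re-check is a change to an endpoint in an open-label trial. It is best done by someone who does not see the allocation. The case report forms are not shown, so it is not known whether survived ventricular fibrillation and times of onset can be recovered for patients already enrolled. No new patient assessment is needed from here on, and the sample size does not change.

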### Population

Patients will be recruited from the First Affiliated Hospital of Shantou University Medical College, 3000 beds of teaching hospital in Guangdong, China, which performs more than 4000 interventional cardiac operations and treats about 800 patients with AMI every year. Patients who may qualify for the study will be screened by a research team consisting of clinicians who are familiar with AMI diagnosis and treatment. The research team consisted of emergency physicians, cardiac intensive care unit physicians, and cardiologists, all of whom are trained in all relevant information about the study. Patients who met the criteria will be actively mobilized to participate in the study from the emergency room to the cardiac intensive care unit or cardiology ward, thereby increasing the enrollment rate.

### Inclusion criteria

Patients eligible for enrollment will be men and women, 18 years of age or older, who are diagnosed with AMI. Diagnostic criteria for AMI were determined according to the Fourth Universal Definition of Myocardial Infarction [14].

A patient with elevated cardiac biomarkers (mainly cTnT) above the 99th percentile of the upper limit of the reference value and who meets at least one of the following conditions is considered to be diagnosed with AMI.Ischemic symptoms.Electrocardiograph has typical manifestations.Echocardiography showed segmental abnormal ventricular wall motion.Intravascular thrombosis confirmed by coronary angiography or autopsy.

### Exclusion criteria

The following are the exclusion criteria:Breast-feeding or pregnant women (pregnancy tests will be performed on women of child-bearing age prior to enrollment)Patients who need probiotics for diarrhea or have used microecological preparations within 1 monthPatients with intolerance to microecological preparationsPatients with immunodeficiency or who have long-term use of immunosuppressive agentsPatients who have stable or unstable angina pectoris that did not fully develop to myocardial infarction

### Withdrawal criteria

Participants will withdraw from the study for any of the following reasons:Patients who experience serious adverse events (AEs) throughout the trialParticipants with poor compliance and could not cooperate with clinical examination and follow-upPatients who quit this clinical trial voluntarily

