### Interventions

Both groups will receive necessary treatments, such as interventional therapy/thrombolysis and medication for coronary heart disease (including but not limited to dual anti-platelet therapy, AECI/ARB, beta blockers, lipid-lowering drugs). Participants will be randomly assigned in 1:1 to either a probiotic group (bifidobacteria triple live bacteria capsules, 840 mg twice a day) or a control group (without bifidobacteria triple live bacteria capsules) during the hospitalization, for a maximum of 30 days. Each probiotic capsule contains active *Bifidobacterium longum*, *Lactobacillus acidophilu*s, and *Enterococcus faecalis*, with the concentration of each bacterium being 1 × 10^7^ CFU/210 mg. During the study period, patients or their guardians will be instructed to record their daily medication as required to ensure compliance. The drug will be discontinued when patients incur severe adverse reactions or required to withdraw from the trial. A brief overview of the study process is provided in Fig. 1. Bifidobacteria triple live bacteria capsules will be provided by Shanghai Xinyi Pharmaceutical Co., Ltd. (Shanghai, China).

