### Follow-up

During the informed consent period, the researcher will have the patient consider whether they can complete the follow-up and then decide whether to participate in the study. In order to facilitate participant retention and complete follow-up, addresses and phone numbers of participants and their families will be collected after consent was obtained. In addition, we will request the physician in charge who is trusted by the patient to assist in the follow-up of the patient. The follow-up period will be divided into two phases, during hospitalization and after discharge. According to statistics, the average hospitalization time of patients with AMI in the First Affiliated Hospital of Shantou University Medical College was 10 days. During hospitalization, the staff will be scheduled to follow up daily, mainly to understand the occurrence of adverse events and the compliance of patients with medication, for a maximum of 30 days. Patients who have been hospitalized for less than 30 days will be followed up by phone or face-to-face on day 30, mainly to check the patient’s survival status and any readmission within 30 days. If there is a readmission within 30 days, further information on the reason for the admission and the presence of adverse cardiovascular events will be obtained. The detailed study schedule is listed in Table 1. Patients who completed the 30-day follow-up were considered to have met the clinical and trial requirements. Patients who discontinued the study drug prematurely will be marked as off-study drug/on study and will follow the same schedule of events as those patients who continue study treatment.

**Table 1 Tab1:** Timeline of trial procedures and follow-up schedule

Study period															
	Screening	Baseline	Follow-up												
Time point (days)	− 1	0	1	2	3	4	5	6	7	8	9	10	etc	30th	Close-out
Eligibility check	X	X													
Informed consent	X														
Relevant medical history taken	X	X													
Physical examination	X	X	X	X	X	X	X	X	X	X	X	X	X	X	
Full blood count		X							X			X		X	
Lipid levels		X							X			X		X	
Liver and renal function		X							X			X		X	
Myocardial enzymes		X							X			X		X	
C-reactive protein		X							X			X		X	
Pro-BNP		X							X			X		X	
HBALC		X							X			X		X	
Electrocardiogram		X							X			X		X	
Echocardiography		X							X			X		X	
All-cause death		X	X	X	X	X	X	X	X	X	X	X	X	X	X
MACE		X	X	X	X	X	X	X	X	X	X	X	X	X	X
Serious adverse events		X	X	X	X	X	X	X	X	X	X	X	X	X	X

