### Statistical and analytical plans

The analyses will adhere to intention-to-treat (ITT) principles. The ITT population included eligible patients who had been randomly assigned to participate in the study, regardless of whether any patients were taking a trial drug. Missing observations are accounted for using the predictive mean matching (PMM) method. Descriptive statistics will be used to analyze the results. Continuous data, such as age, height, and weight, will be presented as mean ± SD. Categorical data such as all-cause death, previous disease history, and smoking history will be expressed as frequency and percentage of patients in each category. Comparison baselines will be obtained using an independent sample *t* test. For the primary outcome, the chi-square test will be used to compare the all-cause mortality in both arms. Secondary outcomes will be assessed by the chi-square test for event rate, and the paired *T* test for quantitative secondary endpoints to compare both treatment arms. In addition, Kaplan–Meier curves will be calculated for visualizing the cumulative events in both groups during hospitalization. A *p*-value of less than 0.05 (*p* < 0.05) will be considered statistically significant. SPSS (25.0) will be used for statistical analysis.

The efficacy and safety of probiotics in the treatment of acute myocardial infarction are unknown. The purpose of interim analyses is to enable early detection of trial safety, early detection and termination of the study in the event of safety problems, and early detection of efficacy, which can be halted for efficacy if the trial is effective and has satisfied prespecified criteria. For interim analysis, we will do a group sequential statistical design with 2 interim analysis when we collect 33% (856) and 67% (1815) of the analyzable patients. The interim analysis will be performed using the Pocock method. Each analysis, including the final analysis, will be set at the same significance level alpha = 0.022 to maintain an overall significance level of 0.05. An independent Data Monitoring Committee supported by an independent, unblinded statistical center will regularly review safety data as well as the interim efficacy analysis.

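### A serious adverse event is a reason to leave the study, which conflicts with the off-drug/on-study rule and with intention-to-treat and puts the mortality outcome at risk of informative loss

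*Protocol article*

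**What the plan says.** All sections are in the protocol article.

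- **Withdrawal criteria:** "Participants will withdraw from the study for any of the following reasons:Patients who experience serious adverse events (AEs". The text does not restrict this to events attributed to the capsule. The same list contains voluntary exit from the trial, and patients who both comply poorly and cannot cooperate with examination and follow-up.
- **Interventions:** "The drug will be discontinued when patients incur severe adverse reactions or required to withdraw from the trial". A severe reaction and withdrawal from the trial appear as two separate triggers for stopping the drug.
- **Follow-up:** "Patients who discontinued the study drug prematurely will be marked as off-study drug/on study and will follow the same schedule of events" as patients still on treatment.
- **Statistical and analytical plans:** "The analyses will adhere to intention-to-treat (ITT) principles". The population is all eligible randomised patients, "regardless of whether any patients were taking a trial drug". For gaps in the data: "Missing observations are accounted for using the predictive mean matching (PMM) method".
- **Outcome measurements and Primary outcome:** inpatients are followed daily until a primary event or discharge, and each patient's survival is tracked by telephone and electronic record. The primary outcome is in-hospital all-cause death at 30 days.
- **Blinding:** nobody is blinded, including outcome assessors and analysts.

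**The concern.** A patient who has a serious event cannot both leave the study and remain in it on the same schedule. The Interventions section separates leaving the trial from stopping the capsule, so the withdrawal rule cannot safely be read as meaning drug discontinuation only.

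The conflict matters because of the endpoint. The Background itself says that events such as heart failure and arrhythmia after infarction carry a substantially higher risk of death. If a serious non-fatal event triggers exit, patients at raised risk of dying are those whose later outcome may go unrecorded. The same holds for later MACE and for safety events such as sepsis. Staff who know the allocation judge whether an event is serious and whether the patient leaves, so the rule could be applied differently in the two arms.

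Intention-to-treat keeps such patients in the analysis set but does not supply their outcome. Predictive mean matching borrows values from patients with observed outcomes. Under a literal reading those donors are mostly patients who had no withdrawing event, so the imputed mortality would tend to be too low.

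**Working it through.** **Step 1. The plan's own sample size.** Inputs from the Sample size section: 8.9% versus 5.34%, two-sided alpha 0.05, power 90%, log-rank test by Freedman's method, 15% dropout.

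- HR = ln(1 − 0.0534) / ln(1 − 0.089) = 0.5887
- Events = (1.960 + 1.282)² × ((1 + HR)/(1 − HR))² = 156.8
- n per arm = 156.8 / (0.089 + 0.0534) = 1101.2, rounded up to 1102
- With dropout: 1102 / 0.85 = 1297 per arm; 2 × 1297 = 2594

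The stated 1102, 1297 and 2594 reproduce. The fault here is not in the arithmetic.

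**Step 2. Power with every outcome known.** For the planned chi-square comparison with n per arm,

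power = Φ[(d − 1.960 × SE0) / SE1],

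where d = p1 − p2, SE0 = √(2p̄(1 − p̄)/n) and SE1 = √((p1(1 − p1) + p2(1 − p2))/n).

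With n = 1297: d = 0.0356, p̄ = 0.0712, SE0 = 0.01010, SE1 = 0.01007, giving Φ(1.569) = 94.2%. Expected deaths are 1297 × 0.089 = 115 and 1297 × 0.0534 = 69.

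**Step 3. Equal loss of deaths (illustration).** Let a fraction f of deaths in each arm follow a withdrawal and go unrecorded. The documents do not give f; 30% and 50% are assumptions. For simplicity only future deaths are removed. There are two ways to treat the lost patients:

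- (a) counted as survivors: the observed rate is p(1 − f), with n = 1297;
- (b) dropped: the rate is p(1 − f)/(1 − pf), with n = 1297(1 − pf).

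| f | (a) observed rates | (a) power at 0.05 | (b) observed rates | (b) power at 0.05 |
|---|---|---|---|---|
| 0 | 8.90% vs 5.34% | 94.2% | 8.90% vs 5.34% | 94.2% |
| 30% | 6.23% vs 3.74% | 83.1% | 6.40% vs 3.80% | 84.7% |
| 50% | 4.45% vs 2.67% | 68.7% | 4.66% vs 2.74% | 71.8% |

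Check of one cell, (a) at f = 50%: d = 0.0178, SE0 = 0.007276, SE1 = 0.007268, Φ(0.487) = 68.7%.

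The dropout allowance does not cover this. At f = 50% the lost deaths are about 1297 × 0.0445 = 58 and 1297 × 0.0267 = 35, together 93 of 2594 patients (3.6%). That is far below 15%, yet it costs over 20 points of power because the loss falls on the events.

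**Step 4. Type I error (illustration).** Set true mortality to 8.9% in both arms.

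- Equal loss, for example 40% in each arm: the observed rates are equal, so the rejection rate stays at the nominal 5% (2.5% in favour of probiotics).
- Unequal loss, 10% of probiotic deaths and none of the control deaths, lost patients dropped: 8.08% versus 8.90% observed, rejection rate 11.6%.

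The imbalance in the second case is an assumption. It shows the direction of the effect, not its likely size.

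**The case against.** The strongest reply is that deaths would be found anyway. The trial has one centre and the endpoint is in-hospital death, so a patient with shock or sepsis would ordinarily stay in that hospital and a death would stand in its own record. The Primary outcome section tracks each patient's survival with no exception for withdrawn patients. Daily follow-up is described as running to a primary event or discharge, not to a serious event. The Serious adverse events section also has patients followed after an adverse event, though only to symptom resolution or the end of treatment. This stands as far as it goes: loss of deaths is a risk, not a certainty. But no section says that any of this continues after withdrawal from the study, and the reply covers later MACE and safety events less well than deaths.

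It can also be said that the off-drug rule governs the drug, the withdrawal rule governs the study, and withdrawn patients formally stay in the analysis set. That is correct. The conflict lies in the outcomes that may go missing, not in an express exclusion from analysis.

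Two stronger readings are tempting and are not supported:

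- **About 40% of patients would be withdrawn.** A reader might infer this from the Background, where "the incidence of heart failure after acute myocardial infarction during hospitalization ranged from 40.2 to 40.5" per cent. It would require every heart failure to count as a withdrawing serious event. Table 1 lists MACE and serious adverse events in separate rows and collects MACE to day 30 and close-out, so that reading would defeat the trial's own secondary endpoint.
- **The compliance criterion acts mainly in the probiotic arm**, since controls have no capsule to take. The criterion joins poor compliance to inability to cooperate with examination and follow-up, and both of those apply in both arms.

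**Conclusion.** The point holds as a conflict in the text. The serious-event limb of the withdrawal rule is incompatible with the off-drug/on-study rule and undermines the stated intention-to-treat analysis. Taken literally it permits informative loss of the primary outcome in an open-label trial, and predictive mean matching would not correct that.

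Confidence is high for the contradiction. The size of any bias cannot be derived from the documents. The fall in power from 94% to 83–85% or 69–72% rests on assumed losses of 30% and 50% of deaths, equal in both arms, at the 0.05 level used in the sample size calculation. A reader might go on to infer that the trial will produce a false benefit. The documents do not support that: equal loss leaves type I error at its nominal level, inflation needs unequal loss, and no section indicates an imbalance. It should still be corrected, because the article reports that recruitment is under way and each withdrawal under this rule may cost a primary outcome.

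**What to change.** - Amend the Withdrawal criteria so that a serious adverse event does not end study participation or outcome collection, and so that only withdrawal of consent ends follow-up.
- State that vital status, MACE and safety outcomes are collected to day 30 for every randomised patient and analysed as randomised.
- For patients already withdrawn under the present rule, recover survival status where consent allows.
- Reconcile the Withdrawal criteria, Interventions, Outcome measurements, Primary outcome, Follow-up and statistical sections with one another. When the capsule is stopped is for the sponsor to decide.

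The cost is a short amendment with ethics approval, plus record retrieval for those already withdrawn. Daily inpatient follow-up and the day-30 contact already exist, so no new visits are needed and the sample size of 2594 does not change.
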